## Participant Selection

### *Inclusion Criteria*

SHARP CENTRAL Registry concerns adult patients ( $\geq 18$  years) with severe asthma in the Europe. Severe asthma is defined according to international ERS/ATS guidelines (16). Briefly, this includes all adult asthma patients with uncontrolled symptoms for at least 6 months despite treatment with medium/high doses of inhaled corticosteroids, with or without oral corticosteroids, in combination with at least one other controller medication (e.g. long acting beta-2-agonists, theophylline), and having been checked for adherence to the medications, inhalation technique and co-morbid factors. These patients qualify for additional treatments for severe asthma, such as biologics. Some patients will already be using these therapies. Patients must be capable of giving informed consent and be able to travel to office/hospital for study visits.

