**[To be completed once every year by case-manager]**

Is patient lost to follow-up?

- ☐ yes
  - ☐ Patient passed away
  - ☐ Patient changed email address
  - ☐ Patient withdrew consent
  - ☐ Other \_\_\_\_\_
- ☐ No

Date of examination (dd-mm-yyyy):

Height: \_\_\_\_\_ cm  
 Weight: \_\_\_\_\_ Kg  
 BMI: \_\_\_\_\_ Kg/m^2

Smoking Status:

- ☐ Never Smoker[SEP]
  - ☐ Ex-Smoker (Quit smoking >12 months)
  - ☐ Current Smoker
- Current number of Pack years: \_\_\_\_\_

Has patient ever been admitted to ICU for asthma?

- ☐ Yes
- ☐ No

If yes, total number of ICU admissions:  
Has patient ever been intubated due to asthma?

- ☐ Yes
- ☐ No

If yes, total number of intubations:

Has the patient ever attended rehabilitation

- ☐ Yes
  - How often? \_\_\_\_\_ times
  - Last time \_\_\_\_\_ years ago
- ☐ No[SEP]
- ☐ Unknown

Has the patient ever undergone bronchial thermoplasty?

- ☐ Yes  
Date/year \_\_\_\_\_
- ☐ No[SEP]
- ☐ Unknown

Has spirometry ever been performed (If done multiple times, please report most current result)[SEP]

- ☐ Yes
- ☐ No

If Yes, when was most recent pulmonary function test performed? (dd/mm/yyyy)

If Yes, which values are available?

- ☐ Pre-bronchodilator values
- ☐ Post-bronchodilator values

|          | PRE
BRONCHODILATOR |                | POST
BRONCHODILATOR |                |
|----------|-----------------------|----------------|------------------------|----------------|
| FEV1     | L                     | %
predicted | L                      | %
predicted |
| FVC      | L                     | %
predicted | L                      | %
predicted |
| FEV1/FVC | %                     |                | %                      |                |

Has exhaled NO testing ever been performed?

- ☐ Yes
- ☐ No

If yes, please report date of most recent result:

FeNO \_\_\_\_\_ppb

Has CO diffusion capacity been performed (ever)?

- ☐ Yes
- ☐ No

If yes, please report date of most recent result:

DLCO: \_\_\_\_\_ mmol/min/kPa and \_\_\_\_\_ % predicted

Has bodyplethysmography (body box) ever been performed?

- ☐ Yes
- ☐ No

If yes, please report date of most recent result:

TLC: \_\_\_\_\_ L and \_\_\_\_\_ % predicted

RV: \_\_\_\_\_ L and \_\_\_\_\_ % predicted

Has bronchial provocation testing with methacholine ever been performed ?

- ☐ Yes
- ☐ No

If yes, please report date of most recent result:

- ☐ Positive (BHR demonstrated, FEV1 decline  $\geq 20\%$ )

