- ☐ Negative (BHR not demonstrated, FEV1 decline  $< 20\%$ )

Has blood cell differential counting been performed in the last 5 years?

- ☐ Yes
- ☐ No

If yes, please report date of most recent result:

- Leukocytes: \_\_\_\_ x 10E9 and \_\_\_\_ %
- Neutrophils: \_\_\_\_ x 10E9 and \_\_\_\_ %
- Eosinophils: \_\_\_\_ x 10E9 and \_\_\_\_ %

If yes, what was the highest eosinophil count ever measured?

Has blood glucose or HbA1c been measured during the last year?

- ☐ Yes
- ☐ No

If yes, please report date of most recent result:

Fasting glucose level:

Hba1c level

Has Blood Gas Analysis been performed/

- ☐ Yes
- ☐ No

If yes, please report date of most recent result:

pH \_\_\_\_\_ pCO2: \_\_\_\_\_ kPa / \_\_\_\_\_ mmHg; pO2: \_\_\_\_\_ kPa /  
\_\_\_\_\_ mmHg;

Has total serum IgE testing been performed?

- ☐ Yes
- ☐ No

If yes, please report date of most recent result:

\_\_\_\_\_ IU/ml or kU/l

Has a routine allergy test RAST/CAP or skin prick testing even been performed?

- ☐ Yes, positive
- ☐ Yes, negative
- ☐ No

If yes, please report date of most recent result:

Has allergy to aspergillus ever been tested?

- ☐ Yes, positive
- ☐ Yes, negative
- ☐ No

If yes, please report date of most recent result:

Has allergy to food ever been tested?

- ☐ Yes, positive
- ☐ Yes, negative
- ☐ No

If yes, please report date of most recent result:

Has sputum analysis (cell counts) ever been performed?

- ☐ Yes
- ☐ Yes, but inadequate sample
- ☐ No

If yes, please report date of most recent result:

\_\_\_\_\_ % Eosinophils  
\_\_\_\_\_ % Neutrophils

Has sputum culture been performed during last year?

- ☐ Yes, positive for pathogens
- ☐ Yes, negative for pathogens
- ☐ Yes, throat bacteria
- ☐ No

If yes, please report date of most recent result:

Has Chest X-Ray ever been performed?

- ☐ Yes, findings compatible with asthma[LSEP]
- ☐ Yes, findings compatible with other pulmonary disorders
- ☐ Yes, normal findings
- ☐ No

If yes, please report date of most recent result:

Has Chest HRCT ever been performed

- ☐ Yes

☐ No

If yes, please report date of most recent result:

- ☐ Bronchiectasis[L]  
[SEP]
- ☐ Emphysema
- ☐ Tree-in-bud configurations
- ☐ Other pulmonary abnormalities
- ☐ No abnormal findings

Has DEXA-scan ever been performed

- ☐ Yes, pathological findings
- ☐ Yes, normal findings
- ☐ No

If yes, please report date of most recent result:

Has bronchoscopy ever been performed

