    - salmeterol \_\_\_\_\_ µg/day and Fluticasone propionate\_\_\_\_\_ µg/day
  - beclomethasone / formoterol
    - beclomethasone \_\_\_\_\_ µg/day and formoterol \_\_\_\_\_ µg/day
  - fluticasone / formoterol
    - fluticasone \_\_\_\_\_ µg/day and formoterol \_\_\_\_\_ µg/day
  - fluticasone furoate/ vilanterol[SEP]
    - fluticasone fuorate \_\_\_\_\_ µg/day and vilanterol \_\_\_\_\_ µg/day
- ☐ Fixed LABA/LAMA combination inhaler
  - indacaterol / glycopyrronium
    - indacaterol \_\_\_\_\_ µg/day and glycopyrronium\_\_\_\_\_ µg/day
- ☐ montelukast
- ☐ theophylline
- ☐ Maintenance oral corticosteroids
  - predniso(lo)ne[SEP]\_\_\_\_\_ mg/day
  - dexamethasone \_\_\_\_\_ mg/day
  - betamethasone \_\_\_\_\_ mg/Day
  - hydrocortisone \_\_\_\_\_ mg/Day
  - triamcinolone (injections) \_\_\_\_\_ mg/month

Is patient currently tapering his/her oral/systemic corticosteroid dose?

- ☐ Yes
- ☐ No

Is the patient currently being treated with biologic therapy?

- ☐ Yes, omalizumab

Start date: dd/mm/yyyy

Dose per injection visit\_\_\_\_\_ mg

Frequency of dosing\_\_\_\_\_ weeks

Has omalizumab dose or interval been changed in last 12 months:

- ☐ Yes, because of adverse effects
- ☐ Yes, because of insufficient response
- ☐ Yes, because of (very) good response
- ☐ No

- ☐ Yes, mepolizumab

Start date: dd/mm/yyyy

Dose per injection/visit\_\_\_\_\_ mg

Frequency of dosing\_\_\_\_\_ weeks

Has mepolizumab dose or interval been changed in last 12 months:

- ☐ Yes, because of adverse effects
- ☐ Yes, because of insufficient response
- ☐ Yes, because of (very) good response
- ☐ No

- ☐ Yes, reslizumab

Start date: dd/mm/yyyy

Dose per infusion/visit\_\_\_\_\_ mg

Frequency of dosing\_\_\_\_\_ weeks

Has reslizumab dose or interval been changed in last 12 months:

- ☐ Yes, because of adverse effects
- ☐ Yes, because of insufficient response
- ☐ Yes, because of (very) good response

☐ Yes, dupilumab

Start date: dd/mm/yyyy

Dose per injection/visit\_\_\_\_\_ mg

Frequency of dosing\_\_\_\_\_ weeks

Has dupilumab dose or interval been changed in last 12 months:

- ☐ Yes, because of adverse effects
- ☐ Yes, because of insufficient response
- ☐ Yes, because of (very) good response
- ☐ No

☐ Yes, benralizumab

Start date: dd/mm/yyyy

Dose per injection/visit\_\_\_\_\_ mg

Frequency of dosing\_\_\_\_\_ weeks

Has benralizumab dose or interval been changed in last 12 months:

- ☐ Yes, because of adverse effects
- ☐ Yes, because of insufficient response

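### Steroid exposure at sampling is not recorded for blood eosinophils, FeNO or sputum cells: maintenance status is unknown for results before or far from a visit, and short courses and exacerbation status for all

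*Protocol*

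**What the plan says.** In the annual case-manager section of Appendix 1, three biomarkers are taken from past records with wide look-back windows:

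- Blood differential: "Has blood cell differential counting been performed in the last 5 years"
- FeNO: "Has exhaled NO testing ever been performed"
- Sputum cells: "Has sputum analysis (cell counts) ever been performed"

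Each is followed by "If yes, please report date of most recent result", and the annual record carries its own "Date of examination (dd-mm-yyyy". Under the blood differential the form also asks "If yes, what was the highest eosinophil count ever measured".

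The medication block is limited to what the patient takes now. For maintenance oral corticosteroids it records drug and dose (per day, or per month for triamcinolone injections), then asks "Is patient currently tapering his/her oral/systemic corticosteroid dose". Each current biologic has a start date and each past biologic a date of last administration. The list of past add-on treatments names biologics, immunosuppressants and others, but not oral corticosteroids.

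The Inclusion Criteria in section 2 admit patients "with or without oral corticosteroids", so mixed steroid exposure in the cohort is expected.

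**The concern.** The Primary Objective is to describe phenotypical characteristics and response to treatment, and the Secondary Objectives section adds clinical predictors of therapeutic response. Eosinophils and FeNO are natural inputs to both. On the assumption, which is general clinical knowledge and not stated in the protocol, that systemic steroids lower eosinophils and can lower FeNO, a result can be interpreted only with the steroid exposure at the time of the sample. The form instead sets a possibly old result beside today's maintenance dose.

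Two errors can follow. A low value taken on steroids, in a patient who has since stopped, can be read as low without steroids. A high value taken before steroids, in a patient now on them, can be read as high despite steroids. The Statistical Analysis Plan section leaves analysis to each project, but no project plan can recover an exposure that was never collected.

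**Working it through.** The protocol gives no figure to reproduce here. The check compares the form's fields and works out the timing gaps.

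**1. What is dated and what is not**

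| Item | Look-back | Dated? |
|---|---|---|
| Blood differential | 5 years | Yes |
| FeNO | Any time | Yes |
| Sputum cells | Any time | Yes |
| Highest eosinophil count | Any time | No |
| Current biologic | Now | Start date |
| Past biologic | Past | Last administration |
| Maintenance oral steroid | Now | No |
| Tapering | Now | No |
| Past oral steroid | No field | – |
| Short steroid course | No field | – |
| Exacerbation at sampling | No field | – |

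A sample can thus be placed after the start of a current biologic or before it, but not relative to maintenance steroids.

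**2. Largest gap between sample and recorded steroid dose**

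- Sample before enrolment: no earlier dose record exists. The gap is up to 5 years for blood and unlimited for FeNO and sputum.
- Sample after enrolment: the Data Collection Schedule sets annual assessments with a tolerance of 1 month either way. If each visit is timed from baseline, two consecutive visits are at most (24 + 1) − (12 − 1) = 14 months apart, so the nearest recorded dose is at most 14 / 2 = 7 months away. If one visit is missed, the interval can be (36 + 1) − (12 − 1) = 26 months and the nearest dose 26 / 2 = 13 months away.
- Under Enrolment, current medications are collected yearly while additional diagnostic tests follow standard of care. An old result can therefore recur beside each new dose.

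**3. Pairs of patients the form cannot separate**

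- Patient A was on maintenance steroids when a low count was taken within the 5-year window and stopped before enrolment. Patient B never took them. Both show a low latest count and no current oral steroid. The highest-ever count may separate them if A was once high; it does not if A's only counts were taken on steroids.
- Patient C had a high count before starting steroids and takes them now. Patient D had the same high count while already on them. Both read as high with current steroids, and the highest-ever count does not help.
- Patient E had a sample on the visit day soon after a short course, with no maintenance dose. Patient F had no steroid at all. Their steroid entries are the same, however recent the sample.

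**4. Other possible sources on the form**

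Health care utilization is entered only as a mean score, so short courses cannot be rebuilt from it. A tick for a steroid-induced adverse effect shows past exposure but is undated.

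**The case against.** The best counter-case is that the form holds more than the look-back windows suggest. Results and examinations are dated, so stale results can be identified and excluded. Maintenance doses recorded at visits on either side of a sample say something about exposure. The highest-ever eosinophil count can reveal past eosinophilia when the latest count is low. The form assigns no phenotype: the protocol sets no eosinophil cut-off or algorithm, and recency rules belong to each project's analysis plan.

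Much of this stands. A reader might infer that suppressed samples can never be told from a true low-eosinophil phenotype, or that analysts have no means of correction. The documents do not support that, because of the three safeguards just named.

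The safeguards are still incomplete:

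- Excluding old results loses data where the old result is the only one, and does nothing about short courses.
- Yearly doses begin at enrolment and so do not cover the earlier samples used at baseline.
- The highest count is undated, has no treatment status, is asked only when a differential was done in the last 5 years, and has no FeNO or sputum equivalent. A low maximum does not rule out suppression.

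It is also fair to say that, for old samples, added items will often be answered as unknown. That limits the gain but makes the uncertainty visible.

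**Conclusion.** The point holds in a bounded form. Maintenance-steroid status at sampling is unknown for results that predate the first registry visit or lie far from any visit. Short-course exposure and exacerbation status at sampling are unknown for all results. This bears on the primary phenotyping objective and cannot be repaired at analysis.

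Its size can be stated only as a time gap: up to 5 years for blood, no limit for FeNO and sputum, and about 7 months at most for post-enrolment samples when no visit is missed. A reader might be tempted to estimate the proportion mislabelled by multiplying assumed shares who are eosinophilic, on steroids at sampling, and suppressed. That product would measure suppression, not unrecognised suppression: it ignores samples whose steroid status matches the recorded one and patients revealed by the highest-ever count. The protocol gives none of these inputs, so no percentage is offered.

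The conclusion rests on the stated assumption that systemic steroids lower these markers, and on the form as shown, which Forms and data handling describes as complete. It is a cheap improvement to data capture and does not invalidate the registry.

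**What to change.** In Appendix 1:

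- Beside the dated blood differential, FeNO and sputum results, add two tick items: systemic corticosteroids on the sample date or in the 4 weeks before (maintenance / burst / none / unknown), and disease state at sampling (stable / acute exacerbation / unknown).
- For maintenance corticosteroids, add the start date, the date of last dose change and, where stopped, the stop date.
- For the highest-ever eosinophil count, add a date and steroid status.

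The sample-level items need filling in only when a new result is entered, so an old result is not re-coded every year. Phenotype analyses should show results of unknown status separately.

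The information comes from the same chart, with no new test and no change to care. The cost is slightly longer data entry and some unknown answers for old samples. Since enrolment is open-ended, each baseline record entered before the change adds to the gap.

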### Summary of Published Information

The past two decades have seen the creation of several European collaborations focusing on severe asthma, beginning in the late 90s with the Framework Programme (FP)-4 funded project on severe asthma, the European Network For Understanding Mechanisms Of Severe Asthma (ENFUMOSA), a cross-sectional observational study which provided the proof of principle for large collaborations (6). Soon after, a more in-depth project was established, focusing on mechanisms and biomarkers of severe asthma: Longitudinal Assessment of Clinical Course and BIOMarkers in Severe Chronic AIRway Disease (BIOAIR) project, funded by the FP-5 and FP-6

and several national funding bodies (7). More recently, the Unbiased BIOMarkers in PREDiction of respiratory disease outcomes (U-BIOPRED) programme, funded by the EU Innovative Medicines Initiative (IMI) project, sought to provide a step-change in phenotyping of chronic airways disease through the use of multi-dimensional clinical outcomes, 'omics biomarkers and sophisticated lung imaging (8). The shared ambition of all these projects was to improve the definition of airways disease phenotypes in order to enable better targeting of existing drugs and those in development and to improve the understanding of determinants of disease severity, disease progression and risk of exacerbations. These collaborations have produced more than 60 high impact publications in respiratory journals and numerous communications at international meetings. The concept of phenotype and endotypes, defined by shared clinical and underlying mechanistic features, respectively, is accepted both in respect of mechanisms and selection for treatment with biologics, for example anti-IL-5 antibody for eosinophilic forms of asthma (9).

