## Objectives

### *Primary Objective*

SHARP CENTRAL Registry is the central registry of ERS SHARP CRC and primarily designed to collect prospective data on the phenotypical characteristics of patients with severe asthma, treatment strategies and patient responses to treatment, burden of severe asthma across Europe at baseline and during follow-up.

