### *Data Quality*

The data entry forms in CastorEDC contain questions with coded answer categories (check boxes and radio-groups) where possible and input fields for quantitative data with plausible range checks and alerts. Quality control procedures for this research register will also include remote control visits. This means that source data will be verified by randomly selecting register participant

records, and comparing data from the original patient file with data in the electronic database record. If errors are common, data will be completely checked prior to data analysis.

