### **Sample Size Determination**

SHARP CENTRAL registry places no limit on the overall sample size to be collected. However, each project that will be carried out with data from the SHARP CENTRAL Registry defining a specific-read out or endpoint will include a sample size calculation and – if appropriate – a power analysis specific to the objectives of the study.

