## Forms and data handling

A complete CRF is attached in the Appendix. The data are entered electronically via internet-based technology. The SHARP CENTRAL Registry web-portal is separated into several parts with different access rules. Any given site investigator in SHARP CENTRAL Registry is allowed to see only data on study participants under the care of the study site to which the site investigator is affiliated. SHARP CRC is allowed to view all data of all centres for plausibility checks, quality control and monitoring. The whole database is saved on a server.

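### The highest-ever eosinophil item in the annual CRF has no unit and hangs on a 5-year condition that does not match it, so entries can mix scales and some patients are never asked

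*Protocol*

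**What the plan says.** The item is in Appendix 1, in the part headed "To be completed once every year by case-manager".

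- The block opens with "Has blood cell differential counting been performed in the last 5 years", answered Yes or No.
- After Yes, the form takes the date of the most recent result, then leukocytes, neutrophils and eosinophils, each with one blank for x10E9 and one for %.
- The next line is "If yes, what was the highest eosinophil count ever measured". It has no unit, no choice between absolute count and percentage, and no date for the peak.

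No other part of the protocol supplies the unit. Registry Data Points mentions blood tests only in general. Forms and data handling states "A complete CRF is attached in the Appendix". Data Quality describes "input fields for quantitative data with plausible range checks and alerts" but names no item, unit or limit.

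The item bears on the main purpose of the registry, which the Primary Objective describes as "primarily designed to collect prospective data on the phenotypical characteristics of patients with severe asthma". Summary of Published Information gives "anti-IL-5 antibody for eosinophilic forms of asthma" as its example of choosing treatment by phenotype.

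**The concern.** Two things about the item do not fit together.

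**Unit.** A bare number directly beneath a two-scale line can be entered on either scale. Most laboratory and lung-function items in this CRF do print a unit (FeNO, DLCO, blood gases, IgE, sputum cells), so the omission does not look deliberate. Fasting glucose and HbA1c in the same section also lack one.

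**Look-back.** The item asks about any time, but its condition looks back only 5 years. Neighbouring items that accept a result from any time, such as spirometry, FeNO, sputum cell counts and HRCT, are opened by a question that also covers any time.

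What is at stake is one phenotype variable. If treatment has lowered the recent count (an assumption, since the protocol does not discuss it), this is the only blood-eosinophil field that can still show an earlier, higher value. Under Data De-identification, Confidentiality, Storage, and Retention, the country databases are exported, anonymised and merged before analysis. An analyst of the merged file would have no stated unit to map and no simple way back to the chart.

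**Working it through.** The protocol gives no figure to reproduce. The check has two parts.

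**1. Size of a scale error**

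Inputs:
- Scales offered on the line above: x10E9 (read here as per litre, since the form prints no volume) and %.
- Total leukocytes L: not in the protocol. Assumed 5-10 x10E9/L, with 4-11 x10E9/L as a wider range.

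For an entry x:
- read as an absolute count: x (x10E9/L)
- read as a percentage: (x / 100) × L (x10E9/L)
- ratio of the two: x / [(x / 100) × L] = 100 / L, whatever the value of x

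Results:
- Entry 1.0 as an absolute count: 1.0 x10E9/L = 1000 cells/uL.
- Entry 1.0 as a percentage: 0.01 × 5 = 0.05 to 0.01 × 10 = 0.10 x10E9/L, or 50-100 cells/uL.
- Ratio: 100 / 10 = 10 to 100 / 5 = 20.
- Wider range: 100 / 11 = 9.1 to 100 / 4 = 25. An entry of 2 is then 2.0 x10E9/L, or 0.08-0.22 x10E9/L.

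Any cut-off between 100 and 1000 cells/uL would classify the entry of 1.0 differently under the two readings. The protocol fixes no cut-off, so the number of patients misclassified cannot be derived.

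**2. Can the form's own content settle the scale?**

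- *Range check.* Values in the hundreds point to cells/uL. Values well above low single digits point to a percentage. In an overlap band, taken here as roughly 0.5 to 3 (an assumption), both readings are plausible and one pair of limits cannot tell them apart.
- *Comparison with the dated differential.* A highest-ever count cannot be below the most recent one. For an entry of 1.0 and L of 5-10, a recent count above 0.10 x10E9/L rules out the percentage reading. At 0.05 or below, both readings survive. In between, the answer depends on a leukocyte count the form does not collect for the peak sample. The comparison therefore helps least when the recent count is low.

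**3. Skip logic**

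| Differential in last 5 years | Is the peak asked? | Effect |
|---|---|---|
| Yes | Yes, over any time | Peaks older than 5 years are captured |
| No | No | No historical peak on that form |

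Because the form is repeated yearly, a patient can move from the first row to the second once the last differential is more than 5 years old. Values on earlier forms are not affected. The protocol does not give the proportion answering No.

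**The case against.** The strongest reply is that this is ordinary CRF tidying, and much of that reply stands.

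- The word count suggests an absolute value, and the live electronic field may carry a label or limits that the appendix does not show. Mixing is therefore possible, not demonstrated.
- A reader might infer that the peak is the only CRF evidence of an eosinophilic phenotype. It is not. The form also takes sputum eosinophils and FeNO from any time, nasal polyposis, EGPA, ABPA, eosinophilic pneumonia including past episodes, and current and past biologic use. A patient enrolled before starting a biologic may also have a dated pre-treatment differential in both scales.
- A reader might infer that mixed entries are lost for good. Data Quality provides source verification on randomly selected records, with a complete check before analysis if errors are common. Monitoring research progress also compares patient records with the electronic CRF. These steps and the comparison with the dated differential can recover some entries.
- A reader might infer that the 5-year condition drops older peaks generally. It does so only for patients answering No.
- No endpoint or analysis in the protocol rests on this item; statistical plans are left to each project.

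What the reply does not answer is that the form as written fixes no scale and skips patients to whom its own question applies. The range checks are described only in general terms, and source verification starts from a sample of records.

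**Conclusion.** The fault holds as a minor data-definition point. The item has no unit beneath a two-scale line, and its condition does not match its look-back.

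A scale error on an affected entry is 10- to 20-fold at an assumed 5-10 x10E9/L leukocytes (about 9- to 25-fold at 4-11). It is hard to detect only at low single-digit values, where the scales overlap. How often this happens cannot be derived from the protocol. The skip condition removes the historical peak completely for patients without a differential in the last 5 years. They are probably few in specialist clinics, although that too is an assumption.

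The item is the CRF's only blood-eosinophil field for a historical peak. The protocol does not support the stronger conclusions that units will be mixed, that the eosinophilic phenotype would be lost, or that affected entries are beyond recovery.

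**What to change.** - Give the field a fixed unit, x10E9/L. If only a percentage is known, record it in a separate % field together with the leukocyte count of the same sample.
- Ask the item on its own, outside the 5-year condition, with not known as an allowed answer.
- Query ambiguous entries already made, before the country databases are anonymised and merged, while the pseudonym still leads back to the site.
- Add units to fasting glucose and HbA1c in the same revision.

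The cost is a small change to the electronic form and one skip rule, a short chart look-up for patients without a recent differential, and one query round. Enrolment is ongoing and the form is completed yearly, so any ambiguous entries accumulate until the change is made.

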### *Enrolment*

Prior to the initial visit, the patient will be consented. Initial baseline demographics of age, gender and ethnicity will be collected from clinic records. Medical history will be collected from clinic records and patient interview. Data from physical examination, diagnostic tests, and current medication use will be taken from clinic records. Patients will be asked to complete 6 questionnaires during clinic visits.

Subsequent yearly appointments: vital signs, height, weight, BMI, pulmonary function tests and current medications will be collected. The study subjects will be asked to complete 6 questionnaires either at the clinic, at home or digitally. All additional registry data (e.g. diagnostic tests) will be collected according to standard of care.

If and when the SHARP CRC develops additional questionnaires or diagnostic tests, these will be added but the patient will have the right to opt out of these and continue with only the original set of questionnaires and diagnostic tests.

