- ☐ methotrexate[L][SEP]
- ☐ cyclosporine[L][SEP]
- ☐ azathioprine[L][SEP]
- ☐ cyclophosphamide
- ☐ interferon alpha
- ☐ aspirin desensitization
- ☐ macrolide therapy (>6 weeks)
- ☐ immunotherapy
- ☐ other: \_\_\_\_\_

Which steroid-induced adverse effects were ever objectively diagnosed?

- ☐ Skin bruising / thinning[L][SEP]
- ☐ Weight gain[L][SEP]
- ☐ Cataract
- ☐ Hypertension[L][SEP]
- ☐ Osteoporosis[L][SEP]
- ☐ Diabetes mellitus[L][SEP]
- ☐ Depression[L][SEP]
- ☐ Other: \_\_\_\_\_
- ☐ Other: \_\_\_\_\_
- ☐ Other: \_\_\_\_\_
- ☐ Other: \_\_\_\_\_

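### The glucose/HbA1c item on the case report form asks about any glucose but can hold only a fasting value, with one date for two tests and no printed units

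*Protocol*

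**What the plan says.** The item stands in the yearly case-manager section of Appendix 1 (Case Report Form) of the protocol. It has four parts, in this order:

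- an entry question with one Yes/No for both tests: "Has blood glucose or HbA1c been measured during the last year";
- one date line: "If yes, please report date of most recent result";
- a glucose result labelled "Fasting glucose level", without a unit;
- an HbA1c result, without a unit and without a date of its own.

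There is no field for a non-fasting glucose and no box for fasting status.

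The protocol does not require a fasting sample. Under Enrolment it says: "All additional registry data (e.g. diagnostic tests) will be collected according to standard of care". Registry Data Points likewise takes blood tests from clinic records. Forms and data handling states: "A complete CRF is attached in the Appendix". Data Quality describes "input fields for quantitative data with plausible range checks and alerts" and a comparison of randomly selected records with the source file. At the end of Appendix 1 a separate item asks "Which steroid-induced adverse effects were ever objectively diagnosed", and diabetes mellitus is one of its tick boxes.

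**The concern.** The entry question is wider than the fields it opens. A site whose patient had only a non-fasting glucose in the past year must answer Yes, and then finds no field that fits the result. What happens next depends on how that site reads the form.

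At stake is the meaning of the stored glucose value. Glucose and HbA1c are the only numeric glycaemic data on the form. The country databases are to be merged and mapped to a common data model for federated analyses (Data De-identification, Confidentiality, Storage, and Retention), so a value labelled as fasting will be read as fasting by analysts far from the clinic. Enrolment is open-ended, so the number of such values grows until the form is changed.

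**Working it through.** The protocol states no figure on this point, so there is none to reproduce. The check is to take each testing situation that routine care can produce and see what the form can hold.

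| Tests in the last year | Entry question | Glucose field | HbA1c field | Date |
|---|---|---|---|---|
| Fasting glucose only | Yes | correct | blank | correct |
| HbA1c only | Yes | blank | correct | correct |
| Non-fasting glucose only | Yes | mislabelled or blank | blank | correct if the value is entered; otherwise dates no stored result |
| Glucose, fasting status unknown | Yes | possibly mislabelled, or blank | blank | as above |
| HbA1c and non-fasting glucose | Yes | mislabelled or blank | correct | at most one test if days differ |
| Fasting glucose and HbA1c, same day | Yes | correct | correct | correct |
| Fasting glucose and HbA1c, different days | Yes | correct | correct | one test only |

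Three results follow from the form alone.

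1. **A blank glucose field after Yes is ambiguous.** It can mean that only HbA1c was done, that the glucose was not fasting, or that a fasting value exists but was not entered. Monitoring research progress says missing data will be marked, but not that the reason is recorded. Elsewhere the form does record a reason: the sputum item has an option for an inadequate sample.
2. **A filled glucose field may hold a non-fasting value.** Nothing stored with it allows a check. The form separates measurement states where it intends to, as with pre- and post-bronchodilator spirometry.
3. **One date serves two results.** If both fall within the last year, the date attached to one of them can be wrong by up to about 12 months.

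On units, neighbouring items print them: FeNO in ppb, DLCO in mmol/min/kPa, IgE in two named units, and the item beginning "Has Blood Gas Analysis been performed" in both kPa and mmHg. The glucose and HbA1c lines print none. This is the weaker part, because a value in a different unit can mostly be recognised from its size. Fasting state cannot.

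**Illustration only.** Every input here is assumed; none comes from the protocol. In mmol/L, take fasting values with mean 5.6 and SD 0.8, non-fasting values with mean 6.8 and SD 1.8, both normal, and a cut-off of 7.0.

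- Fasting share at or above the cut-off: 1 − Φ((7.0 − 5.6)/0.8) = 1 − Φ(1.75) = 0.040.
- Non-fasting share: 1 − Φ((7.0 − 6.8)/1.8) = 1 − Φ(0.11) = 0.456.
- If a fraction p of the values in the fasting field is non-fasting, the recorded share is 0.456p + 0.040(1 − p) = 0.040 + 0.416p.
- p = 0.2 gives 0.123; p = 0.5 gives 0.248.

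With the non-fasting mean varied over 6.2 to 7.2 and its SD over 1.5 to 2.2, the range is about 9% to 14% at p = 0.2 and about 17% to 30% at p = 0.5. The fasting mean and SD were held fixed. Each percentage point of misfiled values adds about 0.4 percentage points under the central inputs, so if p is small the effect is small. The documents give no value for p.

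**The case against.** The strongest reply has four parts.

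- **The label is explicit.** Entering a non-fasting value in a field marked as fasting is a site error, and the protocol checks entries against source, with a complete check if errors prove common. This stands in part. The check is a random sample, it helps only where the source states fasting status, and it does nothing for a blank whose reason was never recorded.
- **Storing only fasting glucose is a defensible choice.** This also stands in part. A project on fasting glucose would not use the non-fasting values anyway. But the entry question should then ask about fasting glucose, so that Yes followed by a blank has one meaning.
- **The outcome is captured in other ways.** This stands. HbA1c has its own field and does not depend on fasting state, and steroid-induced diabetes has its own tick box.
- **Units and date are small matters.** This largely stands. The electronic field settings are not shown and may fix the unit, and no stated objective depends on exact timing within the year.

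A reader might go further and infer that the form mismeasures steroid-related hyperglycaemia, or biases a comparison of steroid users with non-users. The protocol does not support this. It defines no hyperglycaemia endpoint and plans no such comparison; endpoints and analyses are left to each project. A differential bias would need steroid users to be tested more often without fasting and those values to be filed as fasting. Nothing in the protocol shows either.

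**Conclusion.** The point holds as a minor flaw in data capture. The item cannot correctly store a non-fasting glucose, cannot explain a blank glucose field after Yes, and cannot date two tests done on different days. These conclusions rest only on the printed form, which the protocol calls complete, and on tests coming from routine care. They assume that the electronic form adds no fasting-status field or second date.

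The consequence is confined to later projects that use the glucose value or need the date of each test. The registry's primary objective is not affected. The size cannot be derived from the document: the 12% and 25% shares above show what misfiling of 20% or 50% would do under assumed distributions, and they are not estimates for this registry. Confidence that the flaw matters in practice is low; confidence that the wording is mismatched is high.

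**What to change.** Replace the item in Appendix 1 and in the electronic form with two separate lines:

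- **Glucose:** measured in the last year (Yes/No), date, value in one fixed unit (for example mmol/L), and fasting status (fasting, non-fasting, unknown).
- **HbA1c:** measured in the last year (Yes/No), date, and value in one fixed unit (for example mmol/mol).

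Projects that analyse fasting glucose should use only values marked fasting. For records already entered, fasting status should be set to unknown unless the source file states it.

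The cost is one edit to the electronic form and a few more entries per yearly visit. No additional test is needed and patient care does not change. Fewer values will count as fasting, but those that do can be trusted as such.
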